#### 2.2.2. Exclusion Criteria

Patients will be excluded from the study if they were diagnosed as having: (1) severe pelvic organ prolapse, (2) serious cardiovascular and cerebrovascular diseases or other life-threatening diseases, (3) malignant tumor threatening patients life, (4) urogenital tract fistula, (5) previous history of anti-UI surgery and medication for UI, (6) no self-care ability and unable to complete the follow-up, and (7) severe UI and chronic urinary retention.

### 2.3. Randomization and Blinding

In this study, patients will be recruited using convenient sampling without randomization. All investigators, other than those conducting recruitments, will be masked in our study.

### 2.4. Informed Consent

All patients will sign the consent forms (two copies) after being fully informed about this study in detail and any questions they had were answered. One copy will be handed over to the patients, while another copy will be stored at the sub-center for unified management.

### 2.5. Intervention

This is an observational prospective cohort study with no intervention to the enrolled patients.

### 2.6. Initial Screening, Assessment, and Follow-Up

After informed consent, participants will be arranged in the hospital in batches. The patients will be received by a team that consists of physicians specialized in the pelvic floor and nurses. All investigators of the team are comparatively fixed and need to be trained by a principal investigator from Peking University People’s Hospital on the research protocol, the inclusive and exclusive criteria, and the questionnaire interviewing. Roleplay on questionnaire interviewing was conducted to have each of the team members interview a provider’s female family member who had no idea about the study, under the supervision of the principal investigator, to confirm that the question was raised using publicly understandable terms and to avoid inducive wording. Questionnaires to the participants will be completed via interview in a doctor’s office at the clinic, which will be specially resettled for allowing participants to be interviewed under a comfortable circumstance so as to avoid answer bias from patient nervousness.

Every participant will be given a unique study ID. Participants’ demographic information, including age, marital status, education level, occupation, BMI, living habits, menstruation, marriage, childbirths, sex life status, and chronic diseases, ect, were collected confidentially. Participants will be primarily grouped according to the questionnaire interview at the enrollment visit by the investigators. Included in the questionnaires are relevant questions regarding inclusive criteria for three types of UI, which were designed according to the UI classification of the International Continence Society [1]. Participants will be included in the SUI group if question 5 is satisfied, in the UUI group if question 6 is satisfied, or in MUI if question 5 and 6 are both satisfied. All the communication between providers and participants during the questionnaire interview will be monitored by the PI and will be fully recorded for quality control analysis.

For grouping the participants, we will grade the disease situation for each of the participants grouped in each of the groups according to the symptoms using the Ingelman-Sundberg Indexing method and International Continence Society standards [1]. Grading criteria are listed in the following form (Table 1): Participants will be excluded if they are graded to have severe UI.

After collecting the above-mentioned data, all participants will completed a gynecological examination, one-hour urinal pad test, pelvic floor electrophysiological examination, uroflowmetry, pelvic floor ultrasound, and morphological examination (Table 2). All the examinations will be conducted by the teams, using the same model instruments to avoid data biases, and data will be recorded on tablets connected to the database. The items to be inspected are as follows:(1)**Gynecological examination** includes uterus, vagina and appendages inspections; pressure inductive testing; bladder neck elevation testing; hand Oxford muscle strength classification testing; pelvic organ prolapse quantification (POP-Q); and one-hour urinal pad testing.(2)**UI questionnaires** concerning International Consultation on Incontinence Questionnaire-Short Form (ICIQ-SF) for investigation of UI frequency, degree, and its impacts on quality of life via 0–21 scoring to represent the severity of the UI [22]; OABSS questionnaire for assessment of the symptoms of the participants whose bladders are overactive and the severities of their urinary frequency, nocturia, urinary urgency, and urinary incontinence via scoring 0–15 to indicate the lowest to highest severity [23,24]; and Urogenital Distress Inventory-6(UDI-6) for evaluation of the lower urinary tract dysfunction via scoring 0–24 to present the severity of the urinary incontinence [25,26].(3)**Pelvic floor electrophysiological examination** on an instrument to collect data regarding indicators such as the maximum vaginal dynamic pressure, the vaginal resting pressure, the strength grades of type I and type II muscle, and the fatigue of type I and type II muscle fibers.(4)**Uroflowmetry** on the maximum and average rate of urine flow, urination time, and the urine flow curve.(5)**Pelvic floor ultrasound examination** performed by two attending doctors who have rich clinical experience of pelvic floor ultrasound for the residual urine, detrusor muscle thickness, bladder neck movement, urethral rotation angle, bladder posterior angle, the shape of the internal urethra opening, the distance from the lowest point of the bladder to the posterior lower edge of the pubic symphysis, levator ani muscle trauma, and levator ani hiatus area in the Valsalva status.(6)**Morphological examination** a study reported that the pelvis architecture was closely related to UI in women, especially pelvic inlet and pelvic outlet diameters as risk factors for UI [27], therefore, we include pelvic floor morphology into the study, which mainly includes the inclination angle of the sacrum and the anterior superior iliac spine, and the pelvic tendency.

Enrollment and participant grouping will be completed after all of the above procedures. Participant follow-up will be conducted for 6 months, 12 months, and 18 months from enrollment by investigators who were trained for each follow-up question. The follow-ups will be conducted by telephone to learn UI progress by inquiring participants’ symptoms in terms of the history of urinary incontinence, the frequency of urine leakage, the urinary syndrome, the usage of urinal pad, and conscious impact on life, and using a manner of questionnaires (ICIQ-SF, OABSS, and UDI- 6) (Table 2). Patients whose situation could not be confirmed as progressive or who struggle to express their symptoms will be requested to return back to the hospital for follow-up. Follow-up will be terminated for participants whose UI symptoms have aggravated upgrading. Rehabilitation guidance will be provided to participants in the termination of follow-up. Follow-up will be continued for participants with no symptom aggravation for no more than three calls in a period of no longer than 18 months.

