### 2.7. Study Endpoint

As there are no internationally accepted criteria for UI progress, we set up a series of criteria for referring literature, using the Ingelman-Sundberg Indexing method and International Continence Society [1] to judge UI progress in our study. The primary endpoint: UI progress will be judged if any of the following criteria are satisfied: For the SUI group, (1) urinary leakage inducive causes a change from coughing and sneezing to running, jumping and fast walking, or from running, jumping and fast walking to postural changes and rest at bed; (2) urinal pad usage changes from unneeded to needed; or (3) the baseline ICIQ-SF score is heightened for ≥4 [28]. For the UUI group, (1) OABSS score upgrades compared with the baseline, or (2) urinal pad usage changes from unneeded to needed. Progress will be confirmed for the MUI group if participants satisfy any of the progressive criteria for the SUI and UUI groups.

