### 2.10. Statistical Analysis and Progress Prediction Model Construction

Data analysis will be done using SAS^®^ 9.3 software (software installation point authorization number: 11202165).

We set up a prediction model based on the Cox regression model. According to univariate Cox regression analysis, risk factors with a *p* value < 0.05 will be selected to enter the model predictive factors, and then the forward method will be used to carry out multi-factor Cox regression analysis to build the prediction model of the UI disease progress, predicting the risk of UI disease progress. The subjects will be randomly divided into training and validation cohorts according to the ratio of 2:1. The discriminative ability of the prediction model will be analyzed through the area under the ROC curve, and the accuracy of the model will be evaluated by the Hosmer–Lemeshow decile chi-square test. The calibration of the ten models will be assessed with the predicted versus observed probability plots, and the discrimination of the models will be assessed with the prognostic separation D-statistic (D-statistic). The bootstrap method will be used to further internally verify the discriminative ability and accuracy of the model. External validation uses different hospitals for spatial validation to evaluate the extrapolation of the model. Moreover, 100 bootstrap random samplings will be performed to generate 100 bootstrap test sets. For each test set, the area under the ROC curve method and Hosmer–Lemeshow deciles will be used in the square test to objectively evaluate the stability and variation range of the model’s discriminative ability and accuracy. 

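### Progress is dated only to a six-month window between calls, but the planned Cox model needs an exact event time; a grouped-time model fits the schedule better

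*Protocol article*

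**What the plan says.** Protocol article, section 2.6, sets the schedule: "Participant follow-up will be conducted for 6 months, 12 months, and 18 months from enrollment", and "for no more than three calls in a period of no longer than 18 months". The calls are the means of detection: "The follow-ups will be conducted by telephone to learn UI progress". Women whose state cannot be settled by telephone "will be requested to return back to the hospital for follow-up"; no timing is given, but a call triggers the visit. Each woman has at most one event: "Follow-up will be terminated for participants whose UI symptoms have aggravated upgrading".

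Section 2.7 defines progress as a change of state since enrolment, for example "OABSS score upgrades compared with the baseline". None of its criteria refers to a date of onset.

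Section 2.10 names the analysis: "We set up a prediction model based on the Cox regression model", with univariate screening followed by forward selection. It does not mention ties, interval censoring or a discrete-time model.

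**The concern.** A woman found to have progressed at month 12, and not at month 6, progressed somewhere in between. Her event time is interval-censored, whereas the named model uses a single observed time. Two things can follow.

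- If the nominal call month is used as the event time, all events fall on three values. Some ways of handling ties this heavy bias the hazard ratios.
- If a call is missed, progress is dated at the next completed call. The woman is then counted as free of progress at a time when she may already have progressed.

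The product is a risk calculator that the Discussion plans to release as an app, and section 2.10 will judge it by calibration plots and Hosmer–Lemeshow tests. Errors in hazard ratios or in early risks therefore go into what users see.

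**Working it through.** **Inputs from the article.** Assessments at 6, 12 and 18 months (2.6); Cox regression (2.10); at most 800 women split 2:1 (2.9, 2.10), so about 800 × 2/3 = 533 in training. The article gives no progress rate and no hazard ratio (HR). Its sample-size figure reproduces at 20% loss (100/0.8 × 1.5 = 187.5, so 188; 150/0.8 × 1.5 = 281.25, so 282) but has no bearing on this point.

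**Assumptions.** One binary factor split 50:50, constant hazards, true HR 2 (1.5 and 3 also tried), 18-month progress of 10% to 65%, calls exactly on schedule.

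**1. Ties on three nominal times**

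Let q0 and q1 = q0² be the probabilities of passing one six-month interval without progress, without and with the factor. They are the same in every interval, so the large-sample estimates are:

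- Breslow: the ratio of interval risks, (1 − q1)/(1 − q0).
- Discrete (logistic) ties: the ratio of interval odds.
- Complementary log-log: ln q1 / ln q0 = 2, the true value.
- Efron: the θ that solves Σj { D1j − Dj ∫₀¹ θ(R1j − uD1j) / [R0j − uD0j + θ(R1j − uD1j)] du } = 0. R and D are the numbers at risk and progressing in interval j, and Dj = D0j + D1j.

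Example with 50% progress: put x = q0³. Then (x + x²)/2 = 0.5 gives x = 0.618, q0 = 0.8518 and q1 = 0.7256.

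- Breslow: 0.2744/0.1482 = 1.85. The log HR is ln 1.852/ln 2 = 0.889 of the truth, an 11% loss.
- Discrete: (0.2744/0.7256)/(0.1482/0.8518) = 2.17, an error upward.

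| 18-month progress | Breslow HR (loss of log HR) | Efron HR (loss of log HR) |
|---|---|---|
| 10% | 1.98 (1.7%) | 2.00 (0.0%) |
| 20% | 1.95 (3.6%) | 2.00 (0.0%) |
| 30% | 1.92 (5.7%) | 2.00 (0.1%) |
| 40% | 1.89 (8.2%) | 2.00 (0.2%) |
| 50% | 1.85 (11.1%) | 1.99 (0.4%) |
| 60% | 1.81 (14.7%) | 1.99 (0.8%) |
| 65% | 1.78 (16.8%) | 1.99 (1.0%) |

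True HRs of 1.5 and 3 give nearly the same percentages (16.6% and 17.4% for Breslow at 65%). At 60% progress the discrete option gives 2.24.

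Simulation with n = 533, 20% loss and true HR 2 agrees. At 60% progress, exact times gave 2.01, Breslow 1.81, Efron 2.00 and complementary log-log 2.01.

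**2. Missed calls**

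Assume 50% progress by 18 months, each call missed with probability 0.2 at random, and progress dated at the next completed call. A woman with no recorded progress is censored at her last completed call. From q0 and q1, the shares progressing in the three windows are 21.13%, 16.27% and 12.60%.

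- Month 6: recorded 0.8 × 0.2113 = 0.1691; at risk 1 − 0.2³ = 0.992; estimated risk 17.0% against a true 21.1%.
- Month 12: recorded 0.8 × 0.1627 + 0.2 × 0.8 × 0.2113 = 0.1640; at risk 0.96 × (1 − 0.1691) = 0.7977; estimated cumulative risk 34.1% against 37.4%.
- Month 18: recorded 0.8 × (0.1260 + 0.2 × 0.1627 + 0.04 × 0.2113) = 0.1336; at risk 0.8 × (1 − 0.1691 − 0.1640) = 0.5335; estimated cumulative risk 50.6% against 50.0%.

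With 20% progress instead, the estimates are 5.8%, 12.6% and 20.3% against 7.2%, 13.9% and 20.0%. The error lies in the assigned date, so the choice of tie method does not remove it.

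**The case against.** - **Cox regression is not itself at fault.** This stands. With Efron ties on the same three times the loss is about 1% at most. A reader might infer from three assessment times and a Cox model that the hazard ratios will shrink, and that the risk score and all predicted risks will be attenuated. The documents do not support that: section 2.10 names no tie method, and the direction depends on it, since the discrete option errs upward. Nor is there a uniform effect on predicted risk. The missed-call error affects the early horizons and has almost gone by 18 months.
- **The article does not say that events are placed on nominal months.** This also stands. If actual call dates are used, ties thin out. Simulation with n = 533, no dropout and dates spread by ±7 days (an assumption) cut the Breslow loss from 5.3% to 1.7% at 30% progress, from 10.4% to 3.1% at 50%, and from 16.9% to 5.5% at 65%. The date would still be that of the call, not of the onset.
- **The bias is small beside sampling error.** This stands for a single coefficient. At 20% progress it is 0.036 × 0.693 = 0.025 against a standard deviation of the log HR of about 0.22. At 60% it is 0.147 × 0.693 = 0.10 against 0.11 to 0.13.
- **Tie options and missed-call rules belong in an analysis plan.** Fair, and their absence from a condensed article is not the complaint. What the article does fix is detection at three calls analysed by a continuous-time model, and a model matched to that schedule costs almost nothing.

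**Conclusion.** The point holds as a mismatch between how progress is ascertained and the model named for it, with consequences that are conditional.

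- **Hazard ratios.** On nominal times, Breslow ties would lose about 2% of the log HR at 10% progress and about 17% at 65%. Efron ties would lose about 1% at most. The higher rates cannot be ruled out, because in the UUI group section 2.7 sets no minimum size for the OABSS rise, but the article states no rate.
- **Early risks.** With 20% of calls missed and 50% progress, the 6-month risk would read about 17% against 21%, whatever the tie method. The missed-call rate is an assumption; section 2.9 gives only an overall loss of 15–20%.

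All this rests on one binary factor, proportional and constant hazards, and missed calls unrelated to progress. It is worth correcting before analysis. It does not invalidate the study.

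**What to change.** In section 2.10:

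- Fit the grouped-time proportional hazards model: complementary log-log regression with a separate intercept for each of the three intervals. Its coefficients are log hazard ratios on the same scale as Cox.
- Use the interval-censored likelihood when a call is missed. For example, a woman who misses month 6 and has progressed at month 12 contributes 1 − S(12), where S(t) is the probability of no progress by month t.
- Assign each hospital recall visit to the window of the call that triggered it.
- Report predicted risks at 6, 12 and 18 months.

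If Cox regression is kept, the minimum is to state which date counts as the event time and to use Efron ties, or exact ties in the continuous-time sense and not the discrete logistic option. This removes the tie bias but not the missed-call error.

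The cost is a few sentences in 2.10 and slightly more analysis work. Standard software, including the planned SAS, can fit the model, and no new data are needed.

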### 2.7. Study Endpoint

As there are no internationally accepted criteria for UI progress, we set up a series of criteria for referring literature, using the Ingelman-Sundberg Indexing method and International Continence Society [1] to judge UI progress in our study. The primary endpoint: UI progress will be judged if any of the following criteria are satisfied: For the SUI group, (1) urinary leakage inducive causes a change from coughing and sneezing to running, jumping and fast walking, or from running, jumping and fast walking to postural changes and rest at bed; (2) urinal pad usage changes from unneeded to needed; or (3) the baseline ICIQ-SF score is heightened for ≥4 [28]. For the UUI group, (1) OABSS score upgrades compared with the baseline, or (2) urinal pad usage changes from unneeded to needed. Progress will be confirmed for the MUI group if participants satisfy any of the progressive criteria for the SUI and UUI groups.

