UI in women is a huge global health problem. Besides affecting women’s quality of life by limiting social activities, productivity, and social and sexual behaviors, it also has significant impacts on medical costs and even increases financial burden on women and society [4,13]. In addition, regarding the psychological impact of UI on women, numerous research works claim that it creates a long-term period of mental suffering, such as depression or anxiety [14,15,16]. However, some scholars have found, through study of female athletes, that UI does not cause depression and anxiety. Such conclusions are most possibly related to the study subjects, namely female athletes, who have an acknowledged relationship between UI and sport, with most suffering mild UI, as well as having a stronger sense of happiness because of their sport, thus UI might not impact their psychological mode [17].

UI as a common public health issue, is a worldwide problem that has not been indicated to most women, and thus not enough attention has been paid to its early diagnosis and treatment. The impacts of mild and moderate to severe UI on quality of life are greatly different. Although mild UI has little impact on quality of life, as it becomes more severe, it will not only worsen quality of life, but will also bring heavy financial burden to the family and society. Therefore, it is important to use early interventions to upgrade patients’ quality of life and reduce the financial burden related to this disease by detecting any risk factors from patients with mild UI, so as to prevent their mild UI from progressing to moderate or severe.

The common interventions for the prevention of UI include lifestyle intervention, pelvic floor muscle training, biofeedback therapy, and electrical stimulation therapy, etc. However, all these interventions lack standard and systematic evaluations of their preventive effectiveness [18,19].

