## Figures and Tables

**Figure 1 ijerph-19-00734-f001:**
[figure not shown]
Study flow chart.

**Table 1 ijerph-19-00734-t001:** Diagnosis criteria for subtypes of UI.

UI Types	Grade	Criteria
SUI grading	Mild	UI appears when coughing or sneezing without the need for a urinal pad
	Moderate	UI appears when running, jumping, or fast walking, and a urinal pad is needed
	Severe	UI appears when changing body position or resting at bed
UUI grading		According to OABSS indicators Question 3 (urgency) has a score of 2 or more, and the total score is 3 or more)
	Mild	3 ≤ score ≤ 5
	Moderate	6 ≤ score ≤ 11
	Severe	Score ≥ 12
MUI grading		According to the grade of SUI and UUI related symptoms, highest grading to be matched

UI: urinary incontinence; SUI: stress urinary incontinence; UUI: urgency urinary incontinence; MUI: mixed urinary incontinence; OABSS: overactive bladder symptom score.

**Table 2 ijerph-19-00734-t002:** Participant baseline screening, assessment, and follow-up schedule.

Characteristics	Baseline			Follow-Up (6 Months, 12 Months, 18 Months)		
	SUI	UUI	MUI	SUI	UUI	MUI
Age (≥60)	•	•	•			
Race	•	•	•			
Marital status	•	•	•			
Educational level	•	•	•			
Mainly physical labor	•	•	•			
BMI	•	•	•			
Parity	•	•	•			
Manner of delivery	•	•	•			
UI during pregnancy	•	•	•			
UI after childbirth	•	•	•			
Menopause	•	•	•			
Sex life	•	•	•			
Drink preference	•	•	•			
24-h Volume of liquid intake (mL)	•	•	•			
Smoking	•	•	•			
Comorbidities	•	•	•			
Chronic cough						
Asthma						
Diabetes						
Constipation						
Pelvic inflammatory disease	•	•	•			
Depression	•	•	•			
Urinary tract infection (last 4 weeks)	•	•	•			
History of gynecological surgery	•	•	•			
Family history of UI	•	•	•			
UI duration (year)	•	•	•	•	•	•
Frequency of urine leakage (time/month)	•	•	•	•	•	•
Symptoms accompaning urine leakage	•	•	•	•	•	•
Using urine pads (per/month)	▲	▲	▲	▲	▲	▲
Impact on life	•	•	•	•	•	•
POP-Q	•	•	•			
Hand test Oxford muscle strength grading	•	•	•			
One-hour urine pad test (g)	•	•	•			
Severity of UI	•	•	•	•	•	•
Mild						
Moderate						
Severe						
Pelvic floor electrophysiology examination	•	•	•			
Uroflowmetry	•	•	•			
Pelvic floor ultrasound	•	•	•			
Morphological examination	•	•	•			
ICIQ-SF score	•	•	•	•	•	•
OABSS score	•	•	•	•	•	•
UDI-6 score	•	•	•	•	•	•
UI progress				▲	▲	▲

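### Section 2.7 has no rule for a woman who acquires the second type of incontinence, so some rises in Table 1 grade are not counted as progress

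*Protocol article*

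**What the plan says.** Women are assigned to the SUI, UUI or mixed (MUI) group at the start. Section 2.6 states: "Participants will be primarily grouped according to the questionnaire interview at the enrollment visit by the investigators", and closes the step before follow-up begins: "Enrollment and participant grouping will be completed after all of the above procedures". The article gives no rule for changing group afterwards.

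Section 2.7 then sets the primary endpoint by group.

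- **SUI group:** a step in the stress trigger, the first being "urinary leakage inducive causes a change from coughing and sneezing to running, jumping and fast walking" and the second going on to position change or rest; or "2) urinal pad usage changes from unneeded to needed; or (3) the baseline ICIQ-SF score is heightened for ≥4". OABSS and urgency do not appear.
- **UUI group:** "For the UUI group, (1) OABSS score upgrades compared with the baseline, or (2) urinal pad usage changes from unneeded to needed". Stress triggers and ICIQ-SF do not appear.
- **MUI group:** "Progress will be confirmed for the MUI group if participants satisfy any of the progressive criteria for the SUI and UUI groups".

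Table 1 grades severity. Its rule for mixed symptoms is "According to the grade of SUI and UUI related symptoms, highest grading to be matched". Table 2 makes severity of UI, ICIQ-SF and OABSS mandatory at every follow-up in all three groups. Pad use carries the symbol that leaves it to the investigator. A rise in Table 1 grade is not itself a progress criterion.

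**The concern.** The article has two measures of worsening, and they can disagree about the same woman at the same call. Table 1 looks across both symptom types. Section 2.7 looks across both only for women who were mixed at enrolment. A woman who worsens by acquiring the other type can therefore be recorded at a higher severity grade and coded as not progressed.

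This is the outcome variable of the prediction model. The Background motivates the work by the wish to find risk factors in mild disease "so as to prevent their mild UI from progressing to moderate or severe", and the Discussion plans an app that warns patients of likely progress. Coding such women as non-events would understate risk along that route. It would also make the meaning of progress differ by group: the same OABSS rise is an event in a woman labelled UUI or MUI and not in a woman labelled SUI.

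**Working it through.** The plan gives no figure for change of type, so there is none to reproduce. The sample size in Section 2.9 does reproduce (100 × 1.5 / 0.80 = 187.5, so 188; 150 × 1.5 / 0.80 = 281.25, so 282), but it plays no part here.

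**Rules, from Section 2.7**

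- S = a step up from an existing stress trigger, or pad unneeded to needed, or ICIQ-SF rise ≥ 4.
- U = OABSS above baseline, or pad unneeded to needed.
- Event: S in the SUI group, U in the UUI group, S or U in the MUI group.

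**Grade, from Table 1**

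- SUI: mild = cough or sneeze, no pad; moderate = running, jumping or fast walking, and a pad; severe = position change or rest, with no pad condition.
- UUI (urgency item ≥ 2): mild = OABSS 3–5; moderate = 6–11; severe = 12 or more.
- Both present: grade = max(SUI grade, UUI grade).

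**Side by side.** The rules were run over baseline OABSS 0–5 (SUI group) and 3–11 (UUI group), ICIQ-SF rises of 0–7, and the pad and trigger states that Table 1 allows. UUI women were taken with OABSS unchanged.

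| Baseline | At follow-up | Table 1 grade | Section 2.7 |
|---|---|---|---|
| Mild SUI, no pad | OABSS 6–11, urgency item ≥ 2; trigger and pad need unchanged; ICIQ-SF up 0–3 | mild to moderate | no event |
| Mild SUI, no pad | as above, OABSS ≥ 12 | mild to severe | no event |
| Moderate SUI, pad | as above, OABSS ≥ 12 | moderate to severe | no event |
| Mild or moderate UUI | leakage on position change or at rest; OABSS not raised; pad need unchanged | to severe | no event |
| Mild UUI, pad already needed | moderate SUI; OABSS not raised | mild to moderate | no event |
| Mild UUI, no pad | moderate SUI | mild to moderate | **event** (pad) |

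In the UUI rows coded as no event, ICIQ-SF may rise by any amount without changing the result. The last row is always caught, because moderate SUI in Table 1 itself requires a pad.

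**Would the MUI rule close the gap?** For the three SUI rows it would, since OABSS has risen. For the missed UUI rows it would do so only if ICIQ-SF also rose by 4 or more. The trigger criterion lists steps from an existing stress trigger, and a woman with pure UUI has none to step from.

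**Conversions that do not raise the grade.** Mild SUI plus new UUI at OABSS 3–5 stays mild. Moderate SUI plus OABSS 3–11 stays moderate. These are not disagreements between Table 1 and Section 2.7.

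The enumeration shows which states are missed, not how often they occur.

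**The case against.** The best defence is that worsening of the existing type and onset of a second type are different outcomes, and that a team may choose to model the first. The Discussion explains how the criteria were chosen, and the limitations concede that they are team-defined and need further work. The phrase about mild disease becoming moderate or severe is background motivation; the stated aim is a model of progress and its related factors. The article also never says in words that criteria stay tied to the enrolment group, and a full protocol could hold a regrouping rule.

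Part of this stands. Fixed grouping is an inference from enrolment-time grouping and the absence of any other rule. But the article states the primary endpoint group by group and reserves the combined set for the MUI group. It nowhere says that onset of a second type is deliberately excluded, and it keeps a severity grade that would count it.

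A reader might infer that no new symptom of the other type is ever an event. The documents do not support that. Pad need applies in both groups and ICIQ-SF in the SUI group, and neither is specific to one type. Any OABSS rise counts in the UUI group.

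It is also fair that the missed states need particular combinations, such as a large OABSS rise with little change in ICIQ-SF. They show that the gap exists, not that it is common.

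**Conclusion.** The point holds as a gap in the endpoint definition, limited to three routes:

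- (a) mild SUI with OABSS reaching 6 or more, or moderate SUI reaching 12 or more, with urgency item at least 2, trigger and pad need unchanged, and an ICIQ-SF rise under 4;
- (b) UUI with new leakage on position change or at rest, OABSS not raised and pad need unchanged;
- (c) mild UUI already needing a pad that reaches moderate SUI with OABSS not raised.

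It rests on reading the groups as fixed at enrolment.

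The size cannot be computed, because no conversion rate is given. A reader might try one: half of 800 is 400 SUI women; if 5–15% convert, that is 20–60; if half meet no SUI criterion, 10–30 events are lost against the planned 100–150. That should not be used. The 5–15% and the second half come from no document, the 15–20% loss to follow-up is ignored, and conversions that leave the grade unchanged are counted. The 100–150 is also a minimum requirement, not the number expected from 800 women. A claim that particular predictors, such as detrusor thickness or bladder-neck movement, will be attenuated by a known amount is likewise unsupported.

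The change is worth making because it removes a disagreement within the primary endpoint at little cost.

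**What to change.** Add one criterion to each group in Section 2.7: *or the Table 1 grade, regraded over both SUI and UUI symptoms at follow-up, is higher than at baseline*. Record which criterion fired, so that type conversion can be reported separately and excluded in a sensitivity analysis.

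Do not instead apply the whole UUI set to every woman. Its OABSS criterion has no threshold, and OABSS also scores frequency and nocturia, so a one-point rise without any change in leakage would become progress in a woman with SUI. As shown above, pooling the two sets would also leave part of the UUI gap open.

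Cost: mainly wording. Severity of UI, ICIQ-SF and OABSS are already mandatory at follow-up. Pad use is discretionary in Table 2 and would have to be recorded at every call, since Table 1 needs it to grade SUI. The endpoint becomes somewhat broader in the SUI and UUI groups. Because Section 2.6 ends follow-up once symptoms have worsened, follow-up would also end for the added events, and the two sections should be worded consistently on this.
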